### Eligibility criteria

3.3

To ensure a homogeneous sample regarding initial disease severity and to minimize the impact of disease heterogeneity, stringent eligibility criteria will be applied, drawing inspiration from successful ALS clinical trials. This approach aims to create a cohort with comparable disease progression rates and functional status at baseline, thereby enhancing the internal validity and interpretability of our findings. Participants will be eligible for enrollment if they meet all the following criteria: Participants must have a confirmed diagnosis of definite or laboratory-supported probable ALS according to the revised El Escorial criteria, including both sporadic and familial cases.

Eligible individuals will be between 18 and 80 years of age, regardless of sex, and will be enrolled only if they are within 24 months of symptom onset, a criterion intended to reduce variability in disease progression rates. Participants must present with mild to moderate disability corresponding to Sinaki–Mulder stages I–III. Additionally, at baseline, they will need to have a total ALSFRS-R score between 30 and 40, with a minimum score of ≥2 on each of the 12 individual items; this combined threshold is designed to capture patients with early to moderate disability, avoiding floor or ceiling effects and ensuring the scale’s sensitivity to change. Participants must have a forced vital capacity (FVC) of at least 50% of the predicted value based on age, sex, and height, and specifically an FVC of ≥80% of predicted values. Eligible individuals should demonstrate residual limb muscle strength of grade 3 or higher on the Medical Research Council (MRC) scale. Furthermore, patients will be classified using King’s ALS clinical stages 1–2 to confirm early functional stages based on clinical evaluation.

Finally, all participants must be capable of comprehending and following basic verbal motor instructions and must provide written informed consent prior to enrollment. These comprehensive criteria, encompassing diagnostic confirmation, disease duration, functional assessment (ALSFRS-R and Sinaki-Mulder), respiratory capacity (FVC), muscle strength, and clinical staging, will be applied at screening and confirmed through two assessments spaced 2 weeks apart. This multi-dimensional approach to baseline assessment will establish a patient cohort with controlled initial disease severity, thereby increasing the likelihood that any observed therapeutic effects reflect true intervention efficacy.

While the initial site of symptom onset (e.g., bulbar, limb,) will not be an explicit inclusion/exclusion criterion for sample homogeneity, it is recognized that the onset lesion place can significantly influence disease progression and phenotypic presentation in ALS. Therefore, this variable will be considered as a potential covariate in statistical analyses to adjust for its influence on treatment outcomes. Furthermore, *post-hoc* subgroup analyses will be conducted, if statistically powered, to explore differential treatment effects across various onset types. This approach will allow for a more nuanced understanding of the intervention’s efficacy across different ALS phenotypes without overly restricting participant recruitment at the outset of the study.

Exclusion criteria include the presence of a gastrostomy tube or the need for invasive ventilation, a history of other neurodegenerative diseases, or neurological conditions that mimic ALS or could interfere with outcome assessments, such as dementia or cervical spondylotic myelopathy. Individuals with significant comorbidities, including cardiac, pulmonary, hematological, endocrine, or psychiatric disorders, will be excluded if these conditions are judged likely to confound trial outcomes or compromise safety. Women who are pregnant or breastfeeding will not be eligible. Additional exclusions include prior participation in another interventional trial within 3 months before screening, and severe or unstable medical conditions that, in the judgment of investigators, would render the patient unsuitable for Tuina therapy or Riluzole treatment.

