### Sample size

3.2

The sample size calculation was primarily based on the ALSFRS-R as the main clinical endpoint, reflecting the study’s primary objective to evaluate functional decline. Calculations were performed using G*Power software (version 3.1.9.7) for an F-test. Based on a projected medium effect size (*f* = 0.35) for the ALSFRS-R, derived from prior research and clinical expectations for interventions in ALS, a statistical power of 90% (1-*β* = 0.9) and a significance level of *α* = 0.05 across three groups, a total sample size of 108 participants was determined to be necessary. This calculation yields an actual power of approximately 0.905, ensuring sufficient power to detect a clinically meaningful effect on the primary outcome.

To account for the inherent heterogeneity of ALS and to enhance the ability to detect moderate effect sizes and explore potential subgroup differences, the final recruitment target has been further adjusted. Considering an anticipated dropout rate of approximately 20% over the 12-month treatment and follow-up period, the required effective sample size of 36 participants per group (108 participants total) necessitates recruiting 45 participants per group. Thus, the total recruitment target for the study is 135 participants (45 participants × 3 groups). This increased recruitment target ensures that, even with expected attrition, the study will retain sufficient power for the primary outcome and will also allow for more reliable detection of moderate effect sizes, thereby enhancing the precision of exploratory subgroup analyses in this complex disease.

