### Statistical analysis

3.8

All analyses will be performed using SPSS version 25.0 and R. Continuous variables will be checked for normality with the Kolmogorov–Smirnov test and summarized as mean ± SD or as median (interquartile range) if not normally distributed. Between-group comparisons will use analysis of variance (ANOVA) or Kruskal–Wallis tests as appropriate, while categorical variables will be expressed as counts and percentages and compared with chi-square or Fisher’s exact tests. The primary endpoint, ALSFRS-R slope from baseline to 12 months, will be analyzed using a mixed-effects model for repeated measures including group, time, and group × time interaction, with baseline score as covariate and unstructured covariance for within-subject correlation. Secondary outcomes such as muscle strength, spasticity, respiratory function, and quality of life will be analyzed with similar mixed-effects approaches, supplemented by post-hoc tests with Bonferroni correction when necessary. For the imaging substudy, changes in SV2A PET SUVR values will be analyzed using the same mixed-effects framework, with multiplicity controlled across primary regions of interest. Correlations between imaging and clinical outcomes will be examined using Pearson or Spearman coefficients depending on distribution. Analyses will follow the intention-to-treat principle, with missing data handled using maximum likelihood estimation under a missing-at-random assumption, and sensitivity analyses performed to test robustness. A two-sided *p* value <0.05 will be considered statistically significant for primary analyses.

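### The primary slope model adjusts only for baseline ALSFRS-R: onset site is left optional and pre-randomisation progression rate is unused, which gives up precision at almost no cost

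*Protocol article*

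**What the plan says.** Three places in the protocol article bear on this.

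- **Section 3.3, Eligibility criteria (onset site).** Onset site does not restrict entry, but the section accepts that it has a marked bearing on progression. It draws the consequence that "this variable will be considered as a potential covariate in statistical analyses", and adds post-hoc subgroup analyses by onset type if power allows.
- **Section 3.3 (homogeneity).** The entry criteria are meant to "create a cohort with comparable disease progression rates and functional status at baseline". Those relevant here are symptom onset no more than 24 months ago, with no lower limit, and a baseline ALSFRS-R total of 30 to 40.
- **Section 3.8, Statistical analysis.** The primary endpoint, the ALSFRS-R slope over the first 12 months, is analysed by a mixed model with arm, time and their interaction, "with baseline score as covariate". Neither onset site nor progression rate appears in it.

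Section 3.1 describes the randomisation and names no stratification factor.

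**The concern.** The primary endpoint is a slope, so differences between patients in speed of decline are a main source of noise in the treatment contrast. A covariate that predicts later slope removes part of that noise. The plan identifies one such variable itself and leaves its use undecided. A second, the rate of decline before randomisation, can be computed for every participant from data needed at screening.

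Baseline score does not stand in for it. Two patients with the same score may have reached it at very different speeds, and the entry rule bounds score and duration separately, never their ratio. At stake is some avoidable imprecision in the primary contrast, and some uncertainty about whether and where onset site will be adjusted for.

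**Working it through.** **1. The plan's own figure.** Section 3.2 gives a "projected medium effect size (*f* = 0.35) for the ALSFRS-R", "a significance level of *α* = 0.05 across three groups" and 90% target power, and concludes that "a total sample size of 108 participants was determined to be necessary". For a one-way F-test the noncentrality is λ = f²N = 0.35² × 108 = 13.23, with 2 and 105 degrees of freedom. Power is 0.9047, and 108 is the smallest balanced total reaching 90%. This agrees with "This calculation yields an actual power of approximately 0.905". Dropout: 36/(1 − 0.20) = 45 per arm, 135 in total. All of this reproduces.

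**2. What the entry rule admits.** Prior rate = (scale maximum − baseline score) / months since onset.

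- *Equal score, onset 6 versus 24 months ago:* ratio 24/6 = 4, whatever the maximum. The 6 months is an assumed shortest duration.
- *Extremes, with an assumed maximum of 48 (the article does not state it):* the slowest rate is (48 − 40)/24 = 0.33 points per month. The fastest is (48 − 30)/m, where m is the shortest duration.

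| Shortest duration m (months) | Fastest rate (points/month) | Ratio to slowest |
|---|---|---|
| 16 | 1.125 | 3.4 |
| 12 | 1.5 | 4.5 |
| 10 | 1.8 | 5.4 |
| 6 | 3.0 | 9 |

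The values 10 and 16 are the median diagnostic lag given in the Introduction. At equal duration the ratio is 18/8 = 2.25. These ratios describe what the rule allows, not the spread expected in the sample.

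**3. Cost if the covariates are useless.** Two covariates that explain nothing reduce the denominator degrees of freedom from 105 to 103, and power goes from 0.9047 to 0.9046. With four such terms it is 0.9044.

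**4. Gain if they are useful.** The share of slope variance explained (R²) is not in the documents, so 10–30% is assumed. The slope model was simulated with 36 per arm, visits at 0, 1, 6 and 12 months, complete data, unstructured covariance and baseline score as covariate. The assumed slope SD was 0.5 per month and the residual SD 2, with one covariate carrying the stated R².

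| R² of slope variance | Variance ratio, main effect only | Variance ratio, main effect and × time | Equivalent N |
|---|---|---|---|
| 10% | 1.00 | 0.93 | 108/0.93 ≈ 116 |
| 20% | 1.00 | 0.84 | 108/0.84 ≈ 129 |
| 30% | 1.00 | 0.76 | 108/0.76 ≈ 142 |

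The ratio compares the variance of the between-arm slope difference with and without the covariate. A main effect shifts a patient's level at all visits alike and leaves the slope contrast unchanged. Only the interaction with time gains anything.

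**The case against.** The strongest reply is that the two sections can stand together. Section 3.3 speaks of statistical analyses in general, not of the primary one. Section 3.8 states a definite primary model and also foresees sensitivity analyses, where onset site could be used. The article is a condensed account, and final covariate lists often sit in an analysis plan that is not shown. This stands as far as it goes. A reader might infer that the primary result could be chosen from adjusted and unadjusted versions after the data are seen. The documents do not show that, because the stated primary model excludes onset site. The point that remains is that this model leaves out a variable the plan itself calls influential, and a better one is available from data already held.

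Other replies also have force:

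- **Progression rate is a choice, not an obligation.** Adjusting for baseline score alone is valid. The proposed rate contains the baseline score, so it adds less than it would alone, and the documents do not say how well it predicts later slope.
- **Comparable progression is stated as an aim, not a guarantee.** Item scores of at least 2, the respiratory and strength limits and the King's stages may narrow the spread further. A 9-fold range should therefore not be read as expected heterogeneity.
- **Chance imbalance under randomisation is not bias.** With 36 per arm, the difference in a covariate's mean between two arms has a standard error of √(2/36) = 0.24 SD, but the unadjusted standard error already allows for this.
- **Silence on stratification in an article does not show that none is used.**

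Finally, one might compute 108/(1 − R²) = 120, 135 and 154 for R² of 10, 20 and 30%. That treats a share of slope variance as a share of the whole variance of the contrast. The contrast also carries measurement error, which these covariates do not remove, so those figures are too high.

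**Conclusion.** The point holds as a matter of efficiency and of an unsettled covariate. The primary model can be improved with two prognostic variables that are already collected, and the entry criteria alone do not deliver the comparable progression rates they aim for.

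The size is modest and conditional. If the covariates explain 10–30% of slope variance, 108 analysed participants behave like about 116–142. That range rests on an assumed slope SD of 0.5 per month, an assumed residual SD of 2 and an R² the documents do not give. If the covariates explain nothing, power changes by about 0.0001. The prior-rate ratios rest on an assumed shortest duration and, apart from the equal-score case, on an assumed maximum of 48.

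A reader might go further and infer that the trial is underpowered or its primary comparison biased. Neither follows. The sample size and power reproduce, and the randomised comparison is unbiased without these covariates. The change is worth making, but leaving it out would not invalidate the trial.

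**What to change.** Before unblinding, amend sections 3.3 and 3.8 so that they agree.

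- In section 3.8, add two covariates to the primary slope model, each as a main effect and × time: onset site (bulbar / non-bulbar), and pre-baseline progression rate, defined as (48 − baseline ALSFRS-R) / months since onset. Confirm the scale maximum of 48 in the text.
- In section 3.3, delete the word *potential* and refer to the model in section 3.8.
- Report the model without the two covariates as a named sensitivity analysis.
- Keep the rule that "A two-sided *p* value <0.05 will be considered statistically significant for primary analyses" and the recruitment target. Neither needs to change on this account.

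The cost is wording in the protocol and analysis plan. Time since onset and baseline score are already needed for eligibility, and onset site needs only to be recorded at baseline for every participant.

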### Interventions

3.4

All participants, regardless of group allocation, will continue standard pharmacological treatment with oral Riluzole at a dose of 50 mg twice daily throughout the study period. Participants in the intervention arm will additionally undergo a structured program of Tuina therapy. This program will consist of sessions delivered over 12 consecutive months (five sessions per week). Each session will last approximately 45 min and will be administered by a certified senior Tuina therapist.

A tailored approach to Tuina therapy is essential for addressing the specific neuromuscular impairments associated with different segments of the body. According to the neuromuscular segmental localization principle in both traditional Chinese medicine and modern neuroanatomy, Tuina therapy can be strategically applied to areas where damage to motor neurons or muscular function occurs. By focusing on specific segments of the body, Tuina can provide precise stimulation that targets the dysfunction of corresponding spinal segments or neuroanatomical regions, optimizing therapeutic outcomes.

In Chinese medicine, this concept of segmental damage aligns with the idea that Qi and blood flow in specific meridians or channels are disrupted as a result of nerve dysfunction. The motor innervation corresponding to each spinal segment directly influences the muscles and joints within its dermatome or myotome. Thus, Tuina can be applied in a targeted manner to specific body segments corresponding to the site of neuronal damage, enhancing the treatment’s efficacy. Tuina therapy should be performed with a focus on the specific body segment affected by ALS, based on the neurological localization of motor neuron degeneration. The following table outlines common neuromuscular segments typically involved in ALS and the corresponding Tuina techniques (Table 2).

**Table 2 tab2:** Tuina therapy techniques for addressing neuromuscular impairments in ALS patients.

Step	Technique	Area of focus	Purpose	Description
1	Head and neck massage	Head, neck, face	Relieve tension	Gentle pressure on key acupoints like Yintang (between the eyebrows), Taiyang (temple), and Fengchi (back of the skull). This promotes blood circulation to relieve headache, tension, and improve neurological function.
2	Shoulder and arm manipulation	Shoulders, upper arms	Reduce spasticity	Kneading, pressing, and rolling to alleviate tight muscles and improve motor function in the upper limbs, crucial for ALS-related muscle wasting.
3	Back and spine technique	Spine, shoulder blades, ribs	Enhance flexibility and circulation	Rubbing and kneading along the back and spine stimulate muscle relaxation and improve respiratory function. Focus on Du Mai (Governing Vessel) acupoints for energy flow and pain relief.
4	Lower limb treatment	Legs, feet, and joints	Improve mobility and circulation	Gentle pressing, kneading, and shaking to stimulate muscle function in the lower extremities, aiding in motor coordination and muscle recovery. Target key acupoints for Qi circulation like Zu San Li (Stomach 36) and Shen Shu (Kidney 23).
5	Abdominal and chest massage	Abdomen and chest	Regulate internal organs, improve breathing	Circular motions on the abdomen to boost digestion and percussion techniques on the chest for respiratory strengthening. This is especially important in ALS patients with respiratory failure.
6	Advanced joint mobilization	Ankles, knees, elbows	Restore function, prevent contractures	Gentle joint manipulation through rotation and stretching to prevent joint stiffness and increase range of motion.

Tuina will be adapted not only to the spinal segment affected but also to the stage of ALS. In the early stages, when ALS predominantly affects upper motor neurons (spasticity, muscle weakness), Tuina techniques should focus on gentle manipulation to alleviate muscle tension and improve joint flexibility. In the advanced stages, when lower motor neuron involvement leads to muscle atrophy and flaccidity, Tuina should emphasize deep tissue stimulation to enhance blood circulation and prevent further atrophy.

The personalization of Tuina based on neuromuscular localization allows for localized stimulation of affected motor neurons through targeted manual pressure, which improves the transmission of neural signals. It also enhances muscle flexibility by mobilizing joints and soft tissues around the affected segment, and activates synaptic plasticity in motor pathways through consistent, targeted application of Tuina, ultimately promoting neuromuscular reorganization.

Tuina therapy should be continuously adapted in response to the patient’s evolving symptoms and neurological feedback. For instance, increased spasticity in the early stages requires techniques focused on muscle relaxation and softening, while muscle wasting in the later stages necessitates techniques aimed at increasing muscle tone and enhancing muscle strength. Regular assessments of the patient’s muscle strength, muscle tone, and joint mobility should guide modifications to the manual techniques used, ensuring they align with the patient’s specific neuromuscular needs. By incorporating neuromuscular segmental localization into Tuina therapy, we can offer a targeted, individualized treatment approach that maximizes therapeutic benefits for ALS patients.

During the consent process, participants will receive a clear explanation of the intervention protocol, including session structure, treatment goals, and the importance of consistent attendance. This information will be reinforced through a participant handbook outlining the treatment schedule, simplified descriptions of Tuina therapy, and contact details for study staff to support adherence and address participant concerns.

Participants assigned to the sham Tuina group will receive a structured program designed to mimic the duration, frequency, and therapist–patient interaction of active Tuina therapy, without applying therapeutic pressure or stimulation of acupoints administered by a certified Tuina therapist trained to deliver both active and sham protocols. The sham intervention will include light, non-penetrating contact such as gentle gliding and static touch performed along non-meridian areas, deliberately avoiding recognized acupoints and therapeutic manipulations. Pressure will be minimal and insufficient to elicit physiological or neuromuscular responses.

To ensure credibility, participants will be informed that they are receiving a form of manual therapy under investigation for its potential effects in ALS, without specifying whether their allocation represents active or sham treatment. Treatment fidelity will be maintained through session checklists, random supervisory observations, and regular therapist training. At selected time points, participants will complete a treatment credibility and expectancy questionnaire to confirm that sham Tuina is perceived as an acceptable intervention.

### Follow-up

3.5

After completion of the 4-week treatment phase, all participants will undergo scheduled follow-up assessments at 6-month intervals over a total duration of 2 years, resulting in four follow-up visits per patient. Follow-up evaluations will include all predefined outcome measures to monitor long-term effects and disease progression, including the ALSFRS-R, manual muscle test (MMT), forced vital capacity (FVC), and other secondary outcomes. Participants who cannot be reached after five consecutive days of contact attempts by the follow-up nurse will be classified as lost to follow-up.

### Outcome measurement

3.6

Each participant will undergo assessments at baseline (T0), immediately after the 4-week intervention, and at follow-up visits scheduled at 6, 12, 18, and 24 months. These repeated measures are designed to capture both short-term effects of the intervention and its longer-term influence on disease progression, functional capacity, and quality of life. The primary outcome is the change in global functional status, measured using the Amyotrophic Lateral Sclerosis Functional Rating Scale–Revised (ALSFRS-R) (8). The ALSFRS-R is a validated, widely used instrument that evaluates functional impairment across bulbar, motor, and respiratory domains. Changes in ALSFRS-R scores from baseline to each assessment point will be analyzed, with the primary comparison defined as the slope of decline from baseline to 12 months between the intervention groups.

Secondary outcomes are designed to capture additional dimensions of therapeutic impact, including disease progression, neuromuscular performance, respiratory function, and patient-reported quality of life. Longitudinal changes in ALSFRS-R across all follow-up visits will provide an index of disease trajectory. Limb function will be evaluated using the Manual Muscle Test (MMT) to assess muscle strength and the Modified Ashworth Scale (MAS) to quantify spasticity. Respiratory function will be assessed using forced vital capacity (FVC), vital capacity (VC), forced expiratory volume in 1 second (FEV1), the FEV1/FVC ratio, peak expiratory flow (PEF), and maximal voluntary ventilation (MVV), standardized to predicted values based on age, sex, and height. Quality of life will be measured using the ALS Assessment Questionnaire-40 (ALSAQ-40), which covers physical mobility, activities of daily living, emotional well-being, and social engagement. Fiberoptic Endoscopic Evaluation of Swallowing (FEES) will be used as the primary method for evaluating swallowing function. FEES is a validated, gold-standard tool that allows real-time visualization of the pharyngeal phase of swallowing. FEES will be used for baseline assessment and regular follow-up evaluations. This will enable us to track the progression of swallowing dysfunction throughout the course of ALS and assess the impact of the intervention on bulbar function. In the nested imaging substudy, presynaptic integrity will be evaluated using ^18^F SynVesT-1 PET at baseline and Month 6, with standardized uptake value ratios (SUVR) in motor system regions serving as mechanistic biomarkers. Exploratory analyses will also examine correlations between synaptic PET changes and clinical measures (ALSFRS-R, respiratory outcomes, MMT, MAS, and ALSAQ-40).

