## Objectives and hypothesis

2

Given the rapidly progressive nature of ALS and the limited benefits of current pharmacological interventions, there is an urgent need for adjunctive strategies that may preserve function and improve patient quality of life. Tuina has been proposed as a supportive intervention that may influence neuromuscular performance and central neural function.

The primary objective of this trial is to evaluate whether Tuina therapy combined with Riluzole can slow the decline of physical function in patients with early-stage ALS, as assessed by changes in the ALSFRS-R. Secondary objectives include determining the impact of the combined intervention on respiratory capacity, muscle strength, spasticity, and quality of life, as well as assessing the overall safety and tolerability of repeated Tuina sessions. Beyond clinical outcomes, the trial will also explore potential neurobiological mechanisms of Tuina. Using presynaptic SV2A PET imaging at baseline and 6 months, the objective is to examine whether functional changes are accompanied by preservation or enhancement of synaptic integrity in motor system regions.

It is hypothesize that Tuina combined with Riluzole will significantly slow functional decline and improve quality of life compared with Riluzole alone or sham Tuina plus Riluzole. Furthermore, it is anticipated that these clinical benefits may be linked to measurable synaptic changes, providing mechanistic evidence for Tuina as a complementary therapy in ALS.

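### The 90.5% power belongs to a three-group omnibus F-test, while the hypothesis is that Tuina beats sham or riluzole alone; the primary pair and its decision rule are not fixed

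*Protocol article*

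**What the plan says.** Four places in the protocol article bear on this.

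- **Section 3.2, Sample size.** The calculation used "G*Power software (version 3.1.9.7) for an F-test", with f = 0.35, 90% power and "a significance level of *α* = 0.05 across three groups". It gives 108 evaluable patients, and the section adds: "This calculation yields an actual power of approximately 0.905". Allowing for 20% dropout, the target is 135. No pairwise slope difference, standard deviation or pattern of means is given.
- **Section 2, Objectives and hypothesis.** Tuina with riluzole is expected to slow decline "compared with Riluzole alone or sham Tuina plus Riluzole". This has a direction and two comparators, and it does not say whether one or both must be beaten.
- **Section 3.6, Outcome measurement.** The "primary comparison defined as the slope of decline from baseline to 12 months between the intervention groups". No pair is named. Section 3.1 uses the singular of that term for the Tuina arm alone, so the plural does not identify a contrast.
- **Section 3.8, Statistical analysis.** The primary model has group, time and their interaction, with two-sided 0.05 for primary analyses. Secondary outcomes get similar models, "supplemented by post-hoc tests with Bonferroni correction when necessary". A separate remark covers multiplicity across PET regions. Neither statement governs the primary contrasts.

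**The concern.** The test that was powered, the hypothesis and the declared primary comparison are not the same thing. An F-test on three groups asks whether the arms differ at all. It does not ask which arm differs or in which direction.

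That matters in this design. Under section 3.4 the sham arm copies the duration, frequency and therapist contact of Tuina, while the third arm has no sessions. Only Tuina versus sham separates the technique from contact and expectation. If both hands-on arms do equally well and riluzole alone does worse, the omnibus test is significant although Tuina adds nothing over sham. Under the loose wording of section 2, a win over riluzole alone could then be presented as confirming the hypothesis. Section 6 concedes that participants and therapists cannot be fully blinded, so this pattern is not far-fetched.

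**Working it through.** **Inputs.** From section 3.2: f = 0.35, alpha 0.05, three groups, 108 evaluable (36 per arm), 20% dropout. From section 3.8: two-sided 0.05. The pattern of means is assumed, because only f is given. The effect size is taken to apply to one slope or change value per patient, because no slope standard deviation is given.

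**1. The plan's own figure.** One-way ANOVA with noncentral F, df 2 and 105, λ = N·f² = 108 × 0.1225 = 13.23. Power is 0.9047, against 0.905 stated. N = 105 gives 0.896, so 108 is the smallest balanced total that reaches 90%. Dropout: 36/0.80 = 45 per arm, 135 in total. The arithmetic is right.

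**2. From f to pairwise differences** (SD = 1, f² = mean squared deviation of the three means).

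- Tuina differs by d from two equal controls: f² = 2d²/9, so d = 3f/√2 = 0.742.
- Sham midway, means D, D/2, 0: f² = D²/6, so D = f√6 = 0.857 for Tuina versus riluzole alone, and D/2 = 0.429 for Tuina versus sham.

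**3. Pairwise power at 36 per arm, two-sided 0.05.** Noncentral t with noncentrality d√(n/2) = d√18, df 70.

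| Assumed pattern | Contrast | d | Noncentrality | Power |
|---|---|---|---|---|
| Sham = riluzole alone | Tuina vs sham | 0.742 | 3.15 | 87.4% |
| Sham midway | Tuina vs sham | 0.429 | 1.82 | 43.4% |
| Sham midway | Tuina vs riluzole alone | 0.857 | 3.64 | 94.8% |

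Using the pooled variance of all three arms (df 105) gives 87.7%, about 44% and 95.0%.

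**4. What the omnibus test picks up.** With means d, d, 0 (Tuina equal to sham, both better than riluzole alone, same f), simulation of 200,000 trials gives omnibus rejection in 90.5%. This is the same as when Tuina alone works.

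**5. Type I error for the two Tuina contrasts**, all arms equal, 36 per arm, by simulation:

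- each at 0.05, no gate, either may win: about 9.0%;
- pairwise tests only after a significant omnibus test, either may win: 4.2%;
- both must win: no adjustment is needed (both are significant in 0.9% of runs).

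**The case against.** The strongest reply is that sections 3.2, 3.6 and 3.8 can be read together as a single omnibus primary test of group by time at 0.05. On that reading the 5% error and the 90.5% power are both correct. This stands. A reader might infer that neither figure is valid, and the documents do not support that: both are valid for the claim that the three arms differ. They do not carry over to the pairwise hypothesis in section 2.

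A reader might also infer that the trial as written has a 9% error rate. That needs ungated pairwise tests with either one sufficient, and the article states no such rule. The wording of section 2 can also mean better than each comparator, and with three groups an omnibus gate would hold the family-wise rate within 5%. Since none of these rules is stated, the fault is an open decision rule, not a demonstrated inflation. Nor is it right that the article has no multiplicity control at all: it has some for secondary outcomes and PET regions.

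A third tempting reading is that Tuina versus sham has only 43% power. Section 3.4 describes a sham too light to produce a physiological response. On that premise the controls are equal and power is about 87%, some 3 points below the stated figure. The 43% depends on one assumed pattern, in which Tuina versus riluzole alone has about 95%.

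Blinded evaluators (section 6) and the credibility questionnaire (section 3.4) reduce the expectation problem but do not remove it.

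Finally, a statistical analysis plan that is not shown may name the contrast. It would not turn the omnibus 90.5% into the power of a pairwise claim. The article itself sets out to define the primary comparison and leaves it ambiguous.

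**Conclusion.** The point holds in this form. The stated power is correct arithmetic for a non-directional three-group test, and that test does not answer the stated hypothesis: it is equally likely to reject (90.5%) when Tuina is no better than sham. The primary pair is not named, and no rule says whether one or both comparators must be beaten or in what order they are tested.

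The power shortfall for Tuina versus sham is small on the protocol's own premise of an inert sham (about 87%). It is large only if sham delivers part of the benefit (about 43% with sham midway, a sensitivity case). The error rate would rise to about 9% only under ungated, either-wins testing. All pairwise figures assume 36 evaluable per arm and f = 0.35 applied to one value per patient. Confidence is high on the mismatch and the ambiguity. The sizes depend on the assumed means and decision rule.

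**What to change.** In sections 3.6 and 3.8, state a fixed sequence:

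1. Primary: difference in 12-month ALSFRS-R slope, Tuina versus sham, two-sided 0.05.
2. Only if that is significant: Tuina versus riluzole alone, two-sided 0.05.
3. Sham versus riluzole alone: descriptive.

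This holds family-wise error for the two Tuina contrasts at 5% without splitting alpha. An omnibus gate or a both-must-win rule would also control it, but the sequence puts the contrast that isolates Tuina first.

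In section 3.2, say that 90.5% refers only to the omnibus test, and give pairwise power at 36 per arm with its assumed means: about 87% for Tuina versus sham with equal controls, about 43% if sham is midway.

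The cost is wording in three sections and a less favourable power statement, with no extra patients. This discloses the lower power and does not restore 90%. Restoring it for Tuina versus sham at 0.05 would take 40 per arm with equal controls (40/0.80 = 50, so 150 recruited) or 116 per arm with sham midway (116/0.80 = 145, so 435 recruited). Section 3.1 says recruitment is under way, so the rule should be fixed before outcome data are seen by arm.
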